### Randomization

#### Sequence generation

Two investigators in our team will be in charge of implementing the random allocation sequence after they get the whole list of registered patients. All these registered patients will be sorted according to the order of Chinese name, then given number “1” and “2” in sequence. The patients with “1” will be assigned to the immediate intervention group and those with “2” to a waitlist control group.

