## Methods/Design

In this study, a randomized, waitlist controlled trial design will be used. The clinical trial registry number is ChiCTR-IOR-14005390.

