#### Allocation concealment

We will not use “treatment” or “control” group to mention the allocation. All the subjects will be told that they will be arranged into two groups to attend the MBSR session separately due to resource limitations. Four investigators will call the subjects to let them know the group to which they belong, either the immediate group or the waitlist group.

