#### Implementation

Following completion of their hospital treatment, BC survivors return home. As part of the newly launched cancer registry system, each community health service center (CHSC) in Shanghai collects BC survivors’ detail information in order to ensure follow-up and to analyze mortality and morbidity rates. Based on the patient lists from CHSC, we will contact these BC survivors directly to recruit potential participants. All participants who are willing to attend this trial will be requested to submit a signed informed consent. After that, all participants who provide an informed consent will then complete a baseline questionnaire for psychometric assessment (Time 0), with the help from investigators. Information about demographic background and health status will also be collected and later verified by a review of hospital charts.

The immediate intervention group will start the program within 2 weeks of randomization. Two certified MBSR psychotherapists will be hired to implement a standard MBSR intervention. Members of the research team will attend each MBSR session to ensure that intervention standards are met.

All subjects will be reassessed after the intervention group completes half of the program (4 weeks into the intervention, Time 1), 8 weeks later (Time 2), and at 6 (Time 3) and 12 months (Time 4) from the beginning of the intervention. Participants in the control group will be given the opportunity to complete the MBSR program after 6 months follow-up. Eight investigators will be in charge of these follow-ups by telephone.

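### The allocation is labelled random, but the rule described is a fixed one (sort by name, number 1 and 2 in turn), with no list lock and no concealment from those who allocate

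*Protocol article*

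**What the plan says.** The label and the procedure stand in different places of the protocol article.

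- **Label.** Methods/Design states: "In this study, a randomized, waitlist controlled trial design will be used". The Abstract (Methods) likewise says that subjects are assigned at random. Sequence generation puts two investigators in charge of "implementing the random allocation sequence after they get the whole list of registered patients".
- **Procedure.** Sequence generation then gives the method: "All these registered patients will be sorted according to the order of Chinese name", "then given number “1” and “2” in sequence". The mapping to arms is fixed in advance: "The patients with “1” will be assigned to the immediate intervention group and those with “2” to a waitlist control group".
- **Concealment.** The section headed Allocation concealment says "We will not use “treatment” or “control” group to mention the allocation", adds that women will be told that two groups attend separately because resources are limited, and ends with the notification step: "Four investigators will call the subjects to let them know the group to which they belong".
- **Recruitment and timing.** Implementation says: "Based on the patient lists from CHSC, we will contact these BC survivors directly to recruit potential participants". Consent follows, then the Time 0 questionnaire, completed with investigators' help. The immediate group starts within 2 weeks of randomisation.

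**The concern.** Sorting by name, numbering in turn and mapping numbers to arms are all fixed operations. No random number, seed, shuffle or random starting point is stated. The word random and the rule cannot both be right. This is not a detail left to a fuller document: the article states the generation method, and a fuller document could make it random only by replacing it.

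Random allocation carries much of the weight here. The outcomes are self-report scales (Psychological assessment; Compliance level with medication treatment). Women know whether they are in the immediate or the waitlist group. Follow-up is done by investigators over the telephone. With no blinding described to protect the comparison, chance allocation is what makes the two arms exchangeable at baseline. The covariates listed under Statistical methods cannot repair selection on unmeasured characteristics.

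The second issue is who can see or move the assignments. Proper concealment keeps the coming assignment from those who enrol and from anyone who could alter the list. The section with that heading deals with the wording used to participants and with notification after allocation.

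**Working it through.** There is no planned figure to reproduce. The check is to count what the written rule can produce and to trace what a change to the list does.

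**Inputs.** Number to allocate: 418 (Abstract) or 429 (Sample size). The two differ, which is a separate matter; both are carried here. The rule is taken from Sequence generation.

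**1. Number of possible allocations of a fixed list.**
- Written rule: the woman at sorted position k gets arm 1 if k is odd and arm 2 if k is even. One list gives 1 allocation, that is log2(1) = 0 bits of randomness. Each woman's probability of immediate MBSR is 0 or 1.
- 1:1 random allocation: C(N, N/2) possibilities, with N/2 rounded down if N is odd.
  - N = 418: log2 C(418, 209) = 413.3, so about 2^413.
  - N = 429: log2 C(429, 214) = 424.3, so about 2^424.
  - Each woman's probability is one half (214/429 or 215/429 when N is odd).

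**2. Does the result depend on reading the numbering as alternation?** If numbering in sequence meant 1 for the first half of the list and 2 for the second, the count would still be 1. The rule is deterministic on either reading.

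**3. Effect of one change before numbering (alternation).** Removing the name at position k moves the N − k names below it up by one, so each changes arm; adding a name has the same effect on those below it. Averaged over a uniformly random position, the share flipped is

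(1/N) × Σ (N − k)/N = (N − 1)/(2N).

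- N = 418: 417/836 = 0.499, or about 208.5 women.
- N = 429: 428/858 = 0.499, or 214 women.

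Moving a name to another position flips the names between its old and new places; exchanging two neighbours exchanges their arms.

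**4. Who could know an arm, and when.** The article supports two readings of the list of registered patients.

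| Reading | Arms knowable at consent and Time 0? | Arms visible to, and alterable by, the allocating investigators? |
|---|---|---|
| Community health service centre list before consent, or any list not locked | Possibly: the order is in the team's hands before or during recruitment | Yes |
| Consented women only, list locked after Time 0 | Largely not: a woman's odd or even position depends on how many consenting women sort before her | Visible: yes. Alterable: only before the lock |

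The article states no lock and does not say which list is meant. It also does not separate the two allocating investigators from recruitment or baseline assessment.

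**The case against.** The strongest reply is that this is not alternation by order of arrival, where the next assignment is always known. Allocation waits until the whole list is in hand, and Implementation describes consent and then Time 0. The natural reading is allocation in one batch after enrolment. A recruiter could not then work out a woman's arm while the list was still growing. This stands, and it limits the point. A reader might infer that allocation cannot be concealed at all, or that selection at consent and baseline is established. The documents do not support either. Both depend on a pre-consent or unlocked list, which the text leaves open.

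A reader might also infer that every arm is predictable and, at the same time, that one late entry would reverse nearly the whole trial. The two do not go together. Full predictability needs a complete, fixed list; a reversal needs a list that is still open or is renumbered. Reversing nearly everyone further needs a change near the top, whereas the average is about half. A withdrawal after allocation flips nobody unless the list is renumbered, and the article does not say that it would be.

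It is also fair to say that the planned t tests, ANCOVA and mixed models are model-based and can be computed without randomisation, and that there is no evident reason why odd or even position in a name-sorted list should relate to prognosis. That too stands. What is lost is the design's guarantee of exchangeability, and the practical risk is handling of the list rather than name order itself. No bias can be quantified from the documents.

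None of this makes the rule random.

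**Conclusion.** The core point holds on the plain text and needs no assumption about which list is meant. The sequence is called random but is deterministic: 1 possible allocation, against about 2^413 to 2^424. As written, the trial is quasi-randomised, which contradicts the Abstract and Methods/Design.

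A narrower statement holds on concealment. No list lock is stated, and nothing hides assignments from the allocating investigators. They can read off every arm and, before numbering, could change arms by adding, dropping or re-ordering a name. One addition or removal flips about half of the 418 to 429 women on average, assuming alternation and a uniformly random position. Foreknowledge or influence at consent and baseline is conditional: possible if the list is the pre-consent one or is not locked, largely absent if it is a locked list of consented women after Time 0.

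This should be corrected before the first allocation, because no later analysis can restore randomisation.

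**What to change.** Replace the allocation rule in Sequence generation, and add the custody and timing steps to Allocation concealment:

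1. Define the list as women who have consented and completed the Time 0 questionnaire, and lock it with a dated record.
2. Assign arms 1:1 to the locked list from a computer-generated random sequence, and state how it is generated.
3. Have the sequence generated and held by someone with no part in recruitment or baseline assessment, and released only after the lock. An existing team member who meets that condition will do.
4. Keep the wording used to participants and the telephone calls, but present them as notification rather than concealment.

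Stratifying by community or district, with the stratum then included in the ANCOVA and mixed models, is a reasonable option but is not needed to cure the defect.

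If the present rule is kept, describe the trial as quasi-randomised throughout, including the Abstract and Methods/Design.

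The cost is about a paragraph of text and a short program, with no extra patients. The one practical condition is that a suitable person is free: the article assigns two investigators to allocation, four to notification and eight to follow-up, without saying whether they overlap or who recruits. Trial status says that the trial had not begun at the time of writing, so at that stage no allocation would have to be undone.

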### Setting and participants

Shanghai will be selected as the site of the study because it has been characterized by a high incidence of BC in China in recent years [35]. Participants in low-income households will be recruited from about 10 different communities from two of Shanghai’s poorer districts: Yangpu (characterized by an inner-city urban poor population of Shanghai origin) and Minhang (characterized by a migrant worker population).

Inclusion criteria are (1) female, (2) with a history of stage 0, I, II, or III BC, (3) within 2 years from the date of BC diagnosis, (4) currently under at least one adjuvant therapy.

Exclusion criteria are (1) current treatment for recurrent BC, (2) a history of schizophrenia or schizo-affective disorder [24], and (3) current alcohol or drug abuse.

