### Intervention

#### MBSR intervention

Subjects assigned to the MBSR intervention group will receive weekly 2-hour sessions conducted by a psychologist certified and trained in MBSR. Class sizes may range from 20 to 30, with 8–10 groups in total. All sessions will be standardized and will follow the training manual to be developed to maintain consistency in the program. A trained psychologist will deliver the intervention. In addition, an observer will monitor the weekly sessions for inter-group consistency by recording the timing and other aspects of the intervention, and the quality of each session will be assessed in a qualitative post-observation report. Subjects will receive a training manual to support home practice of various forms of meditations (sitting meditation, body scan, and walking meditation) and gentle yoga. The training manual included weekly objectives, exercises, and program content related to the content identified below. In addition, the manual will include a daily diary for recording practice activities at home.

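### Allocation from one pooled list leaves balance on district and community to chance, and the 8-week ANCOVA states no covariate for either

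*Protocol article*

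**What the plan says.** Under Setting and participants, women are "recruited from about 10 different communities from two of Shanghai’s poorer districts". One district is "characterized by an inner-city urban poor population of Shanghai origin"; the other is "characterized by a migrant worker population". Under Implementation, women are identified from the patient lists of the community health service centres, so each woman's community is known before allocation.

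Under Sequence generation, two investigators are responsible for "implementing the random allocation sequence after they get the whole list of registered patients". The rule is then given in full: "All these registered patients will be sorted according to the order of Chinese name", "then given number “1” and “2” in sequence", with the ones going to immediate MBSR and the twos to the waitlist. No step is taken by community or district.

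Under Statistical methods, outcomes are compared by simple two-group tests and by ANCOVA for change from baseline to 8 weeks. A random-effects repeated measures model adjusts for age, education, household income, occupation, previous cancer history and household registration (Shanghai or non-Shanghai). Table 1 assigns the two-group tests and ANCOVA to Primary Hypothesis 1 and the repeated measures model to the secondary, long-term hypothesis. The covariate list is attached to the repeated measures model only. District and community are not on it.

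**The concern.** The article names a contrast between its two recruitment districts that could plausibly relate to mental health, quality of life and medication adherence, and then makes no use of it when forming the arms. This is more than a detail left out of a condensed article, because the stated rule is complete and works on a single list.

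The point does not depend on how the sequence is generated. A truly random sequence on the same pooled list would also leave district and community balance to chance. Two things are at stake: how far the arms may differ on a characteristic the article itself singles out, and some precision lost to between-community variation that stays in the error term of the 8-week comparison. The complete list is in hand before allocation, so this is easy to avoid.

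**Working it through.** **Inputs from the article.** 195 per arm, 390 in total, and 10% attrition, giving a target of 429 (Sample size); 418 in the Abstract; about 10 communities and two districts (Setting and participants); 1:1 allocation by alternation (Sequence generation).

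**Assumptions, not in the article.** Ten communities of equal size; two districts of equal size; name order unrelated to community; community explaining 2–5% of outcome variance.

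**The plan's own figure.** 390 × 1.10 = 429, so the target reproduces as 390 plus 10%. Alternating 429 women gives 215 and 214. With 418 it gives 209 and 209.

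**District balance, pooled list.** For a characteristic with 50% prevalence, the standard deviation of the between-arm difference in share is √[0.25 × (1/n₁ + 1/n₂) × N/(N − 1)].

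- N = 429: √[0.25 × (1/215 + 1/214) × 429/428] = 0.048. 95% range: 1.96 × 4.83 = about ±9.5 points.
- N = 418: √[0.25 × (2/209) × 418/417] = 0.049, about ±9.6 points.
- Simulation of 20,000 allocations (N = 429, ten equal communities, five per district) agrees: SD 4.9 points, 95% within 9.6.

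A difference in share of 0.095 shifts an unadjusted effect estimate by 0.095 times the district difference in outcome. As an illustration, take a district difference as large as the 3.4 points used for planning (50.3 − 46.9). The shift is then 0.095 × 3.4 = 0.32 points.

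**Community balance, pooled list.** With about 43 women per community (429/10), the number allocated to MBSR is hypergeometric. Its mean is 43 × 215/429 = 21.6. Its SD is √[43 × (215/429) × (214/429) × (429 − 43)/428] = 3.1, with a 95% range of 15 to 28. Exact 1:1 allocation within such a community gives 21 or 22.

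**Precision.** After 10% attrition, 429 × 0.90 = 386 women remain. If community explains a fraction r of outcome variance, removing it multiplies the error variance by (1 − r), worth about r × 386 women: 0.02 × 386 = 7.7 and 0.05 × 386 = 19.3, or about 8–19. This is an upper figure, because baseline adjustment and the socioeconomic covariates already absorb part of any stable community difference.

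**Class sizes.** The article says "Class sizes may range from 20 to 30, with 8–10 groups in total". If these groups serve the MBSR arm as a whole, 215/10 = 21.5 and 215/8 = 26.9 (for 418: 209/10 = 20.9 and 209/8 = 26.1). All lie within 20–30, so the stated class plan fits.

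**The case against.** Unstratified allocation of more than 400 individuals is a legitimate design. Chance imbalance is not bias, and the standard error already reflects it. That stands: the point concerns assured balance and some precision, not validity.

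The analysis is also not blind to the district contrast. Household registration, measured per woman, comes close to the difference between Shanghai-origin and migrant populations, and income, education and occupation are adjusted for as well. This stands for the repeated measures model. It covers the 8-week ANCOVA only if the same covariates are used there, which the article does not state; a fuller analysis plan may. Registration says nothing about which community a woman belongs to.

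A reader might infer that the arms will in fact be unbalanced. The document supports only that balance is not assured.

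A reader might also infer that some communities would have too few MBSR women for a local class, so that classes fall below 20, women must travel and drop-out rises. The document does not support this. It nowhere says that classes are formed by community or where they are held, and the stated sizes fit the arm as a whole. The Discussion links feared attrition to the burden of the course and lack of early benefit, not to distance or class size. Nor would stratifying guarantee 20–30 per community: with illustrative community sizes of 30 to 55, it would give 15 to 28.

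Finally, alternation down a name-ordered list is deterministic, and that is the more serious defect in the same section. Stratifying alone would not repair it.

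**Conclusion.** The concern holds as a low-cost design improvement. Pooled allocation leaves balance to chance on a contrast the article itself draws. Under equal districts, the between-arm difference in district share has an SD of about 4.8 points, 95% within about 9.5, with either recruitment target giving nearly the same result. Smaller or unequal districts would change these figures somewhat. The treatment comparison is not biased by this.

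The gap is clearest for Primary Hypothesis 1, where the 8-week ANCOVA states no district-related covariate. For the long-term hypothesis it is partly covered by household registration. Community is in neither model. The precision at stake is modest, at most about 8–19 of 386 women, and rests on the assumed 2–5% of variance.

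**What to change.** In Sequence generation, state that a 1:1 random sequence will be generated separately within each community, or at least within each district, from the completed list. Randomly ordering each community's final list and dividing it in half would do; so would permuted blocks. This should be settled in the same edit that replaces name-ordered alternation with a random sequence.

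In Statistical methods, include the stratification factor (community, or district if that is the level chosen) as a fixed factor in both the 8-week ANCOVA and the repeated measures model.

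The cost is a sentence in one section, a factor in two models and up to 9 model degrees of freedom (10 communities − 1) among about 386 women. With 1:1 allocation within community the factor is nearly orthogonal to arm, so little else is lost. No additional patients or staff are needed, and the Trial status section reports that the trial had not begun.

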#### Allocation concealment

We will not use “treatment” or “control” group to mention the allocation. All the subjects will be told that they will be arranged into two groups to attend the MBSR session separately due to resource limitations. Four investigators will call the subjects to let them know the group to which they belong, either the immediate group or the waitlist group.

#### Implementation

Following completion of their hospital treatment, BC survivors return home. As part of the newly launched cancer registry system, each community health service center (CHSC) in Shanghai collects BC survivors’ detail information in order to ensure follow-up and to analyze mortality and morbidity rates. Based on the patient lists from CHSC, we will contact these BC survivors directly to recruit potential participants. All participants who are willing to attend this trial will be requested to submit a signed informed consent. After that, all participants who provide an informed consent will then complete a baseline questionnaire for psychometric assessment (Time 0), with the help from investigators. Information about demographic background and health status will also be collected and later verified by a review of hospital charts.

The immediate intervention group will start the program within 2 weeks of randomization. Two certified MBSR psychotherapists will be hired to implement a standard MBSR intervention. Members of the research team will attend each MBSR session to ensure that intervention standards are met.

All subjects will be reassessed after the intervention group completes half of the program (4 weeks into the intervention, Time 1), 8 weeks later (Time 2), and at 6 (Time 3) and 12 months (Time 4) from the beginning of the intervention. Participants in the control group will be given the opportunity to complete the MBSR program after 6 months follow-up. Eight investigators will be in charge of these follow-ups by telephone.

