### Primary hypotheses

Participants in MBSR would show improvements in mental health, QOL, and medication treatment compliance, relative to control subjects. We predict that MBSR would help reduce psychological distress and increase patients’ ability to monitor negative cognitions and thereby decrease stress.The levels of mindfulness would increase over the course of the 8-week MBSR program, serving as a mediator to positive changes in mental health, QOL, and medication treatment compliance.

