### Secondary hypotheses

MBSR would be an intervention modal with a long-term effect. We predict that at 1-year follow-up, the MBSR group would still show improvements in mental health, QOL, and medication treatment compliance, compared with its baseline levels.

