#### Usual care regimen

Subjects randomized to the waitlisted control group will receive no formal intervention, but will continue to have standard post-treatment clinic visits according to their treatment plans. Additionally, to avoid possible overlap (contamination) with components of the MBSR program, the investigators will specifically ask subjects in the waitlisted control group not to start mindfulness-based practice during the study period.

MBSR intervention will be offered to each usual care subject after 6 months follow-up. They will be provided with a brief orientation to MBSR (BC), a manual on the program, and a 2-month practice class after post-assessment.

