#### Demographic and health history form

Demographic information will be collected, including age, marital status, education, and employment status. Medical records will be reviewed to obtain information regarding age at BC diagnosis, cancer pathology, past and current cancer treatment, and patient’s compliance with treatment. At each assessment, a health history form will be completed by the participants, including questions related to presence of other medical conditions or diseases, current use of prescription and non-prescription medications and supplements, and occurrence of recent illness.

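### The outcome scales appear to change from an assisted questionnaire at baseline to telephone collection at every follow-up, which adds any mode shift to the secondary within-arm change from baseline

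*Protocol article*

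**What the plan says.** The Implementation section of the protocol article describes two ways of collecting data. After giving signed consent, participants "complete a baseline questionnaire for psychometric assessment (Time 0), with the help from investigators". Reassessments of all subjects then follow at 4 weeks, 8 weeks, 6 months and 12 months (Times 1 to 4), and the paragraph closes with "Eight investigators will be in charge of these follow-ups by telephone".

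The hypotheses use these measurements in two ways. The first primary hypothesis is a between-arm statement: "Participants in MBSR would show improvements in mental health, QOL, and medication treatment compliance, relative to control subjects". The secondary hypothesis is a within-arm statement at 1 year: "the MBSR group would still show improvements in mental health, QOL, and medication treatment compliance, compared with its baseline levels". Table 1 assigns the secondary hypothesis to repeated measures analysis. The adjustment variables listed under Statistical methods do not include mode of collection. Under Usual care regimen, "MBSR intervention will be offered to each usual care subject after 6 months follow-up".

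**The concern.** All five outcome instruments are self-report scales. Two are self-rating scales of distress and one asks about medication adherence. An answer spoken to an investigator by telephone may differ systematically from one given on a questionnaire. Here the mode switches between Time 0 and every later time, so within an arm it cannot be told apart from the passage of time.

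The claim of a long-term effect is at stake. If women answer more favourably by telephone, the shift looks like sustained improvement. If they answer less favourably, it hides a real improvement or looks like worsening. No later analysis plan can repair this, because the data will already have been collected in two modes. The problem is separate from caller masking and would arise with fully masked callers.

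**Working it through.** **Reading the passages together**

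| Contrast | Mode on each side | Effect of a common mode shift |
|---|---|---|
| MBSR vs control at 4 weeks, 8 weeks, 6 months | telephone vs telephone, with the same baseline mode in both arms | largely cancels |
| MBSR arm at 12 months vs its own Time 0 | telephone vs assisted questionnaire | added in full to the change |

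A mode covariate would not help in the second row, because within the arm it equals the indicator of baseline versus follow-up. The control arm cannot remove the shift at 12 months either, since by then it has been offered MBSR.

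**Illustration of size**

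The plan gives no figure to reproduce on this point. The inputs are:
- n = 195 in the MBSR arm (Sample size section).
- Correlation r between baseline and 12 months: not given. Assumed 0.5, range 0.4 to 0.7.
- Mode shift d in SD units: not given. Assumed 0.05 to 0.2.
- No true change, equal SD at both times, paired t test at two-sided 5%. This test stands in for the within-arm contrast of the repeated measures model.

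Noncentrality = d × √n / √(2(1 − r)). With n = 195 and r = 0.5, √195 = 13.96 and √(2 × 0.5) = 1, so it equals 13.96 × d. The rejection probability comes from the noncentral t distribution with 194 degrees of freedom.

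| Shift d | Noncentrality (r = 0.5) | Significant change, r = 0.5 | r = 0.4 to 0.7 |
|---|---|---|---|
| 0 | 0 | 5% | 5% |
| 0.05 | 0.70 | 11% | 10% to 15% |
| 0.1 | 1.40 | 28% | 25% to 43% |
| 0.2 | 2.79 | 79% | 72% to 95% |

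Nearly all of these rejections fall in the direction of the shift. At d = 0.1 and r = 0.5, 28.4% fall in that direction and 0.04% in the other.

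**Between-arm check**

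In an ANCOVA of a follow-up value on arm and baseline, a shift common to both arms goes into the intercept and leaves the arm coefficient unchanged. A simulation with 195 per arm, correlation 0.6, no MBSR effect and 2,000 runs agrees. For shifts of 0, 0.1 and 0.2 SD, the within-arm test rejected in 6.0%, 35% and 87% of runs. The between-arm ANCOVA rejected in 6.4%, 4.7% and 5.6%, with no trend as the shift grew (simulation error is about 0.5 percentage points at 5%).

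**The case against.** **The change of mode is partly inferred.** The article does not say that the baseline is on paper or face to face, and investigators' help could include reading items aloud. Being in charge of follow-ups by telephone could mean arranging contacts. This stands as a caveat. The plain reading is still an assisted questionnaire followed by telephone collection, and no follow-up visit is described for telephone calls to arrange.

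**The size is assumed.** This stands in full. The documents give neither size nor direction for a mode shift, so the percentages illustrate sensitivity and do not predict an error rate. A reader might infer from them that the trial is likely to claim a false benefit. The documents do not support that, since the same figures describe false worsening if the shift goes the other way.

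**The planned analysis is not a paired t test.** This is correct. The repeated measures model also uses both arms. But the secondary hypothesis is worded against the arm's own baseline, and any model that answers that question takes the same Time 0 to Time 4 difference.

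**The 12-month comparison is uncontrolled anyway.** This is also correct. Natural recovery and regression to the mean remain whatever the mode, which limits the importance of the point. The mode change is nevertheless a separate source of bias that can be removed.

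**A condensed article may leave procedures to the full protocol.** This is fair for call scripts. The two modes, however, are stated here and not merely omitted.

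Two stronger readings are tempting. One is that the primary between-arm results are biased too; the shared mode at each time argues against that. The other is that the article contradicts itself by saying "At each assessment, a health history form will be completed by the participants". That sentence concerns the health history form, not the outcome scales, and supports neither side.

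**Conclusion.** The point holds in limited form. On the plain reading, mode of collection coincides with baseline versus follow-up, and the secondary hypothesis rests on exactly that difference. Neither the listed covariates nor an untreated 12-month arm can separate the two. Under the stated assumptions, even a 0.05 SD shift roughly doubles the nominal 5% rate of a significant change, and 0.2 SD makes one more likely than not. The true shift may be smaller, or zero. The primary between-arm contrasts up to 6 months are not materially affected, provided that the shift is the same in both arms. The change should be made before recruitment, and the Trial status section says that the trial had not begun.

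**What to change.** Administer SDS, SAS, MAAS, the Quality of Life Index and MMAS in one mode at all five times, with the same script and caller pool. One way is to collect the Time 0 scales by telephone, after signed consent and before randomization, and to leave consent and the demographic form as they are.

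The cost is a change of protocol wording and one scripted call per woman, which the investigators already assigned to telephone follow-up could make. The downside is real. SDS, SAS, MAAS and MMAS have 20 + 20 + 15 + 8 = 63 items, and the two-part, 34-item Quality of Life Index comes on top. The call would be long, and some baseline data could be lost between consent and randomization.

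If Time 0 stays an assisted questionnaire, state the mode at each assessment and do not interpret within-arm change from Time 0 as an effect of MBSR. Base effect claims on between-arm contrasts up to 6 months, and describe 12-month maintenance in the MBSR arm against its 8-week telephone assessment. Under either option, report the 12-month result as an uncontrolled comparison, because a single mode does not make it causal.
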